#### Postoperative data collection and follow-up

After surgery, participating patients will be monitored for postoperative delirium from postoperative day 1 to postoperative day 7, or until they are discharged from the hospital. Following this period, they will be asked to evaluate their cognitive symptoms weekly for up to 3 months after surgery. The questionnaire will be distributed digitally using REDCap (table 2).

At both 1-month and 3-month post-surgery, we will assess neurocognitive function (using the Mindmore-P), self-efficacy, depression and functional capacity. At the 6-month mark (the endpoint of the study), we will also evaluate frailty, fatigue and health-related quality of life. Perioperative data will be collected from the patient’s medical records. Close relatives of the patients will complete the same questionnaires (focused on the cognitive assessment of the relative and caregiver burden) at 1-month, 3-month and 6-month postsurgery. Each follow-up session is expected to take approximately 40–50 min for the patients and about 10 min for the close relatives (table 2).

#### Qualitative interviews

Qualitative semistructured interviews will be conducted approximately 6 months after the surgery with a subsample of participants. Both patients (n≥20) and their close relatives (n≥20) will be invited to participate, and they will be interviewed separately to capture their individual experiences. The estimated number of participants for qualitative interviews is informed by the concept of information power (ie, the expected amount of information required to answer the research question).^44^ We aim to include patients who have experienced cognitive symptoms. To identify these individuals, we have established cut-off scores for persistent cognitive symptom burden. Cognitive symptom burden is assessed using the SwQoR-Cog, with four non-cognitive items removed. The remaining 10 items form the cognitive subscore, ranging from 0 to 100. The threshold for symptom burden is defined as a subscore of ≥30. For inclusion in qualitative interviews, participants must exceed the cut-off (ie, ≥30) measured at 6 and 12 weeks postoperatively. If the patient has undergone another major surgery between the cardiac surgery and the interview, they will not be considered for the interview. Major surgery is defined as a surgical procedure that lasts longer than 1 hour in duration. Participants will have the option to choose the interview location, which can be face-to-face, digital or via telephone. The interviews are expected to last between 30 and 60 min (table 2).

### Data analysis and statistics

Descriptive statistics will be presented, including frequency, percentage, mean, SD or range, as appropriate. We will calculate standardised reliable change Z-scores for each neurocognitive test (n=4) based on the differences in patients' test results from baseline to postoperative assessments, adjusting for variance using Swedish normative data.^45^ In accordance with the guidelines established by Borchers *et al*. in their 2021 review^46^ and Evered *et al*. in their 2018 nomenclature,^10^ we define objective decline in dNCR/p-NCD as mild (1–2 SD) and major (greater than 2 SD) for each test result. This classification requires at least two test results for accuracy.

Parametric and non-parametric tests will be used to identify differences between groups regarding outcomes and demographic characteristics. We will assess potential associations between our dependent variable (neurocognitive performance) and independent variables using multivariate logistic regression analysis. A p value of less than 0.05 will be considered statistically significant in all analyses.

Mixed effect models will be used for the analysis of longitudinal data and potential clustering of data on patient-reported cognitive symptoms. Trajectories of patient-reported cognitive symptoms will be analysed with statistical process control (SPC).^47^ The SPC involves the creation of control charts that are used to evaluate how processes change over time. A pooled SD measure based on the first two trials from SwQoR-Cog will be used for the calculation of control limits. X-bar and S charts will be used for process analysis on group level. Individual processes will be analysed with I-diagrams within SPC.

The SwQoR-Cog and CFQ-f will undergo further psychometric evaluation, guided by the COnsensus-based Standards for the selection of health Measurement INstruments.^48^ Additionally, interviews with patients and their close relatives will be analysed using qualitative content analysis, which is appropriate for exploring and identifying knowledge where evidence is limited.^49^ Finally, we will synthesise both quantitative and qualitative findings to identify similarities and differences, examining whether the qualitative results converge with or diverge from the quantitative findings.^21^

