**Methods and analysis:**

A longitudinal observational study with a mixed-methods approach will be conducted in two thoracic surgical departments in Sweden. A total of 220 patients and 1 close relative for each patient will participate. Neurocognitive function will be assessed preoperatively and at 1, 3 and 6 months postoperatively using a digitalised neurocognitive test battery. We will also evaluate postoperative patient-reported cognitive symptoms and signs, delirium, frailty, health-related quality of life, depression, perceived self-efficacy, fatigue and functional capacity. Each patient’s close relative will assess the observed cognitive function and report on caregiver burden. At the 6-month mark, a purposive sample of patients and their close relatives will be interviewed to explore their experiences of postoperative cognitive recovery.

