## Introduction

 The global population of older adults is increasing rapidly, making this demographic group the fastest-growing worldwide. By 2070, it is projected that one in four people in Sweden will be 65 years or older,^1^ and similar trends can be observed globally.^2^ As cardiovascular disease is one of the most common health issues among older adults, it is anticipated that the number of older adults undergoing cardiac surgery will also rise.^3 4^ Older adults are more susceptible to postoperative complications, which are often medical rather than surgical in nature. They tend to experience longer hospital stays and higher rates of readmission compared with the general population.^5^ Additionally, many older adults face multimorbidity,^6^ and a significant number may be classified as frail,^7^ whether or not they have pre-existing cognitive impairments.^8^

Postoperative neurocognitive impairment is a frequent yet often unrecognised complication following cardiac surgery, which can affect the patient’s recovery, quality of life and daily functioning, as well as impact their close relatives.^9^ Perioperative neurocognitive disorder, previously known as postoperative cognitive dysfunction, is an overarching term used to describe cognitive impairment that occurs post-surgery, reflecting a decline in neurocognitive performance from the preoperative baseline.^10^ This includes postoperative delirium (POD), characterised by a sudden decline in attention and cognitive function occurring within 7 days after surgery, delayed neurocognitive recovery (dNCR), which refers to cognitive dysfunction that persists or arises within 30 days after the procedure, as well as mild or major postoperative neurocognitive disorders (p-NCD) that can be identified up to 12 months after surgery.^10^ To diagnose dNCR and p-NCD, the Diagnostic and Statistical Manual of Mental Disorders, Fifth Edition pillars of diagnosis for neurocognitive disorders^11^ are required: (1) subjective complaint/cognitive symptoms assessed by the patient, a caregiver or a close relative/friend; (2) objective impairment/change assessed by neurocognitive tests and (3) the individual’s functional level related to the activities of daily living.^10^

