### Aim

The purpose of this study is to investigate the factors that influence neurocognitive function and patient-reported cognitive symptoms among patients aged 65 and older following cardiac surgery, and explore the impact on the overall postoperative recovery. Additionally, the study aims to describe the perspectives of close relatives on the recovery process. The following scientific questions will be addressed in the study.

What is the incidence of dNCR/p-NCD and the occurrence of patient-reported cognitive symptoms in older adults up to 6 months after cardiac surgery?Is there a correlation between preoperative cognitive status and dNCR/p-NCD, and if so, which cognitive function (executive function, attention and memory) is most affected?Is there a correlation between POD and dNCR/p-NCD, and if so, which cognitive function is most affected?Which factors (eg, age, educational level, duration of surgery, perceived self-efficacy, frailty and mental health and depression) affect the risk of suffering from postoperative cognitive decline?Is dNCR/p-NCD associated with increased symptom burden, impaired functional level, fatigue, frailty, deteriorated quality of life and an increased number of unplanned contacts with healthcare services?How do older adults with persistent cognitive symptom burden experience their postoperative recovery and return to daily life?How do close relatives to older adults with persistent cognitive symptom burden perceive the patient’s postoperative cognitive function and recovery, and how does this affect the relative’s own life?

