### Participants

Participants in the study will consist of older adults aged 65 years and above who are undergoing open cardiac surgery (eg, bypass grafting or valve replacement or a combination of both). The goal is to include a total of 220 patients, along with one accompanying close relative for each patient. The sample size estimation is based on a statistical power analysis aimed at detecting a 25% rate of dNCR among participants 1 month after surgery, using a normal SD with α=Zα = 1.960 and factoring in a 15% dropout rate.

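### The objective-decline rule flags about 12–16% of unchanged patients at each visit, half or more of the 25% planning rate, and the plan gives no chance benchmark

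*Protocol article*

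**What the plan says.** All references are to the protocol article.

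- **Scores** (Data analysis and statistics): "We will calculate standardised reliable change Z-scores for each neurocognitive test (n=4", which fixes the number of tests at four. Scores are changes from the preoperative test, "adjusting for variance using Swedish normative data".
- **Case rule** (same section): "we define objective decline in dNCR/p-NCD as mild (1–2 SD) and major (greater than 2 SD) for each test result", followed by "This classification requires at least two test results for accuracy".
- **Visits** (Abstract): "Neurocognitive function will be assessed preoperatively and at 1, 3 and 6 months postoperatively".
- **Research question 1** (Aim): "What is the incidence of dNCR/p-NCD and the occurrence of patient-reported cognitive symptoms in older adults up to 6 months after cardiac surgery". Questions 2, 3 and 5 use dNCR/p-NCD as a variable.
- **Planning rate** (Participants): the 220 patients are meant for "detecting a 25% rate of dNCR among participants 1 month after surgery", with 15% dropout.
- **Diagnosis** (Introduction): dNCR and p-NCD need three elements. Besides objective change these are "subjective complaint/cognitive symptoms assessed by the patient, a caregiver or a close relative/friend" and the level of daily functioning. Instruments for both are scheduled in Table 2, but the analysis section defines only the objective element and does not say how the three combine.

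**The concern.** A reliable-change score has a known spread in people who have not changed. A cut at 1 SD on several tests therefore turns a predictable share of stable patients into cases. The study is a single cohort, so no comparison group shows how large that share is. Normative scaling does not remove it: giving the score unit SD is exactly what puts 15.9% of stable patients below −1 on each test.

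Two things are at stake. An objective-decline rate near the planning value could not be read as decline after surgery without knowing what the rule yields by chance. And if false cases arise equally in exposed and unexposed patients, they pull the associations in questions 2, 3 and 5 toward no effect.

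**Working it through.** **The plan's own figure.** The 220 cannot be rebuilt from its stated inputs, because no precision, null rate or power is given. A back-solved half-width of 0.0625 comes close: 1.96² × 0.25 × 0.75 / 0.0625² gives 185, and 185/0.85 gives 218. Below, the 25% serves only as a yardstick, with 220 × 0.85 = 187 evaluable patients.

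**Assumptions.** The four Z-scores have mean 0 and SD 1 in an unchanged patient. A case has at least two of four at or below −1. Correlations between tests and between visits are not in the article and are varied; one shared baseline with equal error variances gives a between-visit correlation of 0.5.

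**One visit, independent tests.** P(Z ≤ −1) = 0.1587, so

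P(at least 2 of 4) = 1 − 0.8413⁴ − 4 × 0.1587 × 0.8413³ = 1 − 0.501 − 0.378 = 0.121.

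**Correlated tests and visits.** Simulation of 400,000 unchanged patients per setting:

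| Between-test r | One visit | Any of 3 visits (visit r 0.5 / 0.7) | Both 3 and 6 months (visit r 0.5 / 0.7) |
|---|---|---|---|
| 0 | 12.1% | 27.6% / 24.8% | 3.4% / 4.7% |
| 0.2 | 14.7% | 31.6% / 28.0% | 5.0% / 6.6% |
| 0.3 | 15.6% | 32.8% / 29.1% | 5.5% / 7.5% |
| 0.5 | 16.9% | 34.5% / 30.6% | 6.5% / 8.6% |

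For r from 0 to 0.3, a visit yields 0.121 × 187 ≈ 23 to 0.156 × 187 ≈ 29 cases if nobody declined. A 25% rate is about 47 cases. The ratios are 12.1/25 = 48% and 15.6/25 = 62%.

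**Major category.** Taking a major case as at least two of four tests beyond 2 SD, chance gives 0.3% (r = 0), 1.0% (r = 0.3) and 1.5% (r = 0.5) per visit. Nearly all chance cases are therefore mild.

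**Share of false cases at an observed 25%.** With chance rate f and sensitivity s, true prevalence is π = (0.25 − f)/(s − f), and the false share is (1 − π) × f/0.25.

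- f = 0.12, s = 0.6: π = 0.13/0.48 = 0.271; share = 0.729 × 0.12/0.25 = 35%.
- f = 0.12, s = 1: π = 0.13/0.88 = 0.148; share = 41%.
- f = 0.16, s = 1: π = 0.09/0.84 = 0.107; share = 0.893 × 0.16/0.25 = 57%.

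**Dilution, as an illustration.** Assume a true odds ratio of 3, 25% exposed and full sensitivity. With f = 0.12 and π = 0.148, the true risks are about 0.267 (exposed) and 0.108 (unexposed). Adding 12% of the non-cases gives 0.355 and 0.215, an observed odds ratio of (0.355/0.645)/(0.215/0.785) ≈ 2.0. With f = 0.14 it is about 1.8.

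**What a benchmark would show.** At 25% of 187 the 95% half-width is 1.96 × √(0.25 × 0.75/187) = 6.2 points. Taking the benchmark as known, the excess is 12.9 points (6.7 to 19.1) over 12.1%, and 9.4 points (3.2 to 15.6) over 15.6%.

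**The case against.** - **The objective element is not the diagnosis.** The Introduction also requires a subjective complaint and a functional criterion. If these are applied, the false rate for full dNCR/p-NCD is lower, by an amount the article does not allow anyone to compute. This stands. It limits the figures to objective decline, and it exposes a gap, since the analysis section does not say whether the other two elements are required.
- **The scaling cannot be verified.** If the normative variance were cross-sectional and retest correlation 0.8 (assumed), the SD of change would be √(2 × 0.2) = 0.63 normative SD. The chance rate would then be 5.7% per test and about 1.8% for two of four. An uncorrected learning gain of 0.2 SD would give 6.8–10.0%, although the Discussion calls learning effects minimal. This stands as a condition on the 12–16%.
- **The rule follows cited nomenclature, and benchmarks are often left to an analysis plan.** This is fair, and the rule need not be replaced. But the article itself fixes the threshold and the test count, and their chance yield follows from them.
- **Incidence over the whole follow-up.** A reader might infer that question 1 counts decline at any visit, with a chance rate of about 25–33%. The article states no such rule. It separates dNCR (within 30 days) from later p-NCD and sizes the study on 1 month alone.
- **The sentence on two test results.** It could be read as two results being available, so that one falling test suffices; chance would then be 1 − 0.8413⁴ = 50% with independent tests. That is the less natural reading, and a reason to clarify the sentence.

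**Conclusion.** The point holds for objective decline at a single visit. With correctly centred Z-scores scaled to retest error and between-test correlation 0 to 0.3, the rule yields about 12–16% cases among unchanged patients, which is about half or more of the 25% planning rate. At an observed 25%, about 35–57% of objective cases would be false, depending on the chance rate and sensitivity assumed.

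A reader might conclude that the reported incidence is largely measurement noise. The documents do not support that. Over much of the range the false cases are a minority, the major category is almost free of them, and the full diagnosis may carry further criteria. The supported conclusion is narrower: the raw objective rate, above all for mild decline, cannot be interpreted without its chance rate, and the associations in questions 2, 3 and 5 would be diluted to the extent that they rest on this definition.

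**What to change.** 1. State the rule as at least two of the four tests each down 1 SD or more. Say whether the subjective and functional criteria are also required for a case of dNCR or p-NCD.
2. Report visit-specific rates with mild and major separate. Beside each, give the rate the same rule yields with no change, taken from the normative or retest sample or from its between-test correlations, and report the excess with a 95% CI.
3. As a sensitivity analysis only, repeat the p-NCD rate and the association analyses for decline present at both 3 and 6 months (chance about 3–7%). It should not replace the main outcome, because it changes what is being estimated.

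The cost is some analysis wording and a short calculation, with no new patients or assessments. The excess will be lower than the raw rate. The sensitivity analysis needs both later visits and drops transient or late-onset decline.

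### Risk factors for cognitive decline are tied to logistic regression alone, although continuous change scores at three visits would carry more information and allow the cognitive domains to be compared

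*Protocol article*

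**What the plan says.** All of this is in the protocol article.

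- **Outcome data.** Table 2 schedules the digital test battery before surgery and at 1, 3 and 6 months. The section Data analysis and statistics turns each of the four tests into a change Z-score against baseline, then grades decline on each test as mild (1–2 SD) or major (more than 2 SD). The classification needs at least two test results.
- **Risk-factor model.** The same section says: "We will assess potential associations between our dependent variable (neurocognitive performance) and independent variables using multivariate logistic regression analysis". It adds: "A p value of less than 0.05 will be considered statistically significant in all analyses".
- **Mixed models.** These have a sentence of their own: "Mixed effect models will be used for the analysis of longitudinal data and potential clustering of data on patient-reported cognitive symptoms".
- **The questions served.** Under Aim, question 4 is about cognitive decline and asks: "Which factors (eg, age, educational level, duration of surgery, perceived self-efficacy, frailty and mental health and depression) affect the risk". Questions 2 and 3 ask whether preoperative cognition and delirium are related to dNCR/p-NCD and, if so, which cognitive function suffers most.
- **Planning figures.** Under Participants: "The goal is to include a total of 220 patients". The target of the calculation is "detecting a 25% rate of dNCR among participants 1 month after surgery"; the critical value given is 1.960, and 15% of patients are allowed for as lost.

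**The concern.** Logistic regression needs a categorical outcome, and the only categories that the section defines are the SD-based grades of decline. The named dependent variable, neurocognitive performance, is measured on a continuous scale. Once it is cut, a patient just short of the threshold counts the same as one who improved, and a patient just past it the same as one with a severe loss. That discards information on which the search for risk factors depends, in a study with a modest number of expected events.

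Two further features of the data go unused in the named model. The scores are repeated at three postoperative visits, and they are separate by test. Questions 2 and 3 turn on differences between functions, and a single label pooled over tests cannot show them.

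At stake is the chance of detecting moderate risk factors, and a direct answer on which function is most affected. The validity of the planned analysis is not at stake.

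**Working it through.** **Inputs from the article.** N = 220; dropout 15%; dNCR rate 25% at 1 month; z = 1.960, that is two-sided 0.05; four tests; three postoperative visits. The Introduction also cites 40–50% early cognitive complications after cardiac surgery, used here as an alternative rate.

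**The plan's own figure.** The article gives neither a precision nor a power with a null rate, so 220 cannot be derived from what is stated. With an assumed 95% half-width of 6.25 points, n = 1.96² × 0.25 × 0.75 / 0.0625² gives 185 after rounding up, and 185/0.85 ≈ 218, close to 220. No event count or power is stated for the regression.

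**Expected events at 1 month.**
- Evaluable: 220 × 0.85 = 187.
- Events: 187 × 0.25 = 46.75, about 47.
- At a 40–50% rate: 187 × 0.40 ≈ 75 to 187 × 0.50 ≈ 94.

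**Information kept after dichotomising.** For a normal score cut so that a proportion q counts as decline, efficiency relative to the continuous score is φ(z_q)² / [q(1 − q)], where φ is the standard normal density. At q = 0.25, z = −0.674 and φ = 0.3178, so the ratio is 0.1010/0.1875 = 0.539.

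| Rate of decline | Information kept | 187 patients count as |
|---|---|---|
| 20% | 0.490 | 92 |
| 25% | 0.539 | 101 |
| 30% | 0.576 | 108 |
| 40% | 0.622 | 116 |
| 50% | 0.637 | 119 |

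**Power.** Simulation with n = 187, one normally distributed risk factor, outcome cut at 25%, two-sided 0.05 and 1,500 replicates. The correlation r between factor and score is an assumption.

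| r | Linear model | Logistic model |
|---|---|---|
| 0.15 | 54% | 33% |
| 0.20 | 79% | 53% |
| 0.25 | 93% | 71% |

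A hand check at r = 0.20 agrees. The expected test statistic is atanh(0.20) × √184 = 0.2027 × 13.56 = 2.75, so power is Φ(2.75 − 1.96) = Φ(0.79) ≈ 79%. Scaling by √0.539 = 0.734 gives 2.02, and Φ(0.06) ≈ 52%.

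**Two extensions, both on assumptions.**
- *Three visits.* If a factor acts equally at each visit and visits correlate at ρ, the mean of three scores carries 3/(1 + 2ρ) times the information of one. This is 1.50 at ρ = 0.5 and 1.07 at ρ = 0.9. A single-visit yes/no outcome then keeps 0.539/1.50 = 0.36 to 0.539/1.07 = 0.50.
- *Composite rule.* If decline means at least two of four tests below −1 SD, with 25% prevalence and inter-test correlation 0 to 0.6, simulation gives 0.37 to 0.50 kept relative to the mean Z-score.

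**The case against.** The strongest reply is that logistic regression fits the questions as worded. Questions 1 to 4 concern a diagnostic category and the risk of decline, and the Introduction says that the diagnosis rests on complaint and daily function as well as test change. A mean change in SD is a different quantity from clinical risk, and an outcome built on all three elements is not simply a normal score cut at its 25th percentile. This stands. It is why the logistic model should remain, and why the 54% describes the test-based part of the definition only.

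It can also be said that the mixed-model sentence may cover longitudinal data in general, the Z-scores included. That reading is possible. But the sentence goes on to patient-reported symptoms, while associations with neurocognitive performance have their own sentence and their own model.

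A reader might infer more than the article supports:
- *That power is halved.* The effective sample size is roughly halved. Power falls by about 21 to 26 percentage points in the simulated cases.
- *That only complete cases are used, that patients missing a visit are dropped, or that three conflicting models will be fitted.* The article states none of this.
- *That the model is overfitted.* Seven factors on 47 events is 6.7 events per variable, and adding preoperative cognition and delirium gives 5.2. But the list in question 4 is given as examples, delirium and preoperative cognition are separate questions, and no covariate set is fixed. Covariate choice may properly be left to an analysis plan not shown here.
- *That domains cannot be compared at all.* Decline is graded test by test and group comparisons of outcomes are planned, so test-level comparisons remain possible. The named regression on a pooled label does not make them.

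**Conclusion.** The point holds as one of efficiency and fit to the questions. The logistic analysis is valid for dNCR/p-NCD, but as the only named model for risk factors it uses about 54% of the information in a single-visit score at the planned 25% rate, and 62–64% if the rate is 40–50%. The first figure makes 187 evaluable patients worth about 101, with about 47 events expected.

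The percentages assume a roughly normal score and a binary outcome; an ordinal model of none, mild and major decline would lose somewhat less. The power figures further assume a single normally distributed factor and the correlations shown. The loss is present at every rate examined. Separately from any power argument, a pooled yes/no outcome does not address which function is most affected. This is a cheap improvement, not a flaw that invalidates the plan.

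**What to change.** Keep logistic regression for the dNCR/p-NCD classification. For questions 2–4, add a linear mixed model of the continuous test or domain Z-scores at 1, 3 and 6 months, with:

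- a patient random effect, with test or domain as a repeated measure and all Z-scores oriented so that the same sign means decline;
- fixed effects for visit, site and the prespecified preoperative and perioperative factors;
- a factor-by-domain interaction, to address which function is most affected.

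Two details belong with it. State which test stands for which of the functions named in question 2, since Table 1 lists executive function against three of the four tests. And reword the mixed-model sentence to say whether it covers the neurocognitive scores. In question 2, baseline performance is also part of the change score, so regression to the mean needs care under either model.

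The cost is wording and slightly more analysis work; no patients, visits or instruments are added. The effects from this model are in SD units, which are less familiar to clinical readers than odds ratios, but the logistic results would still be reported beside them.
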